**Primary objectives:**

- determine the extent of naturally acquired humoral and cellular immune responses to *P. falciparum* and *P. vivax* in children aged 5-10 years.
- determine the association of immune responses with protection against *P. falciparum* and *P. vivax* infection and disease in children aged 5-10 years.

**Secondary objectives:**

- evaluate the effect of clearing liver and blood-stage infections vs clearing blood-stage infections only on cellular and humoral immune responses.
- compare cellular and humoral immune responses to *P. falciparum* and *P. vivax* in children aged 5-10 years from this region of PNG with those from children aged 5-14 years in the Mugil region of PNG.

**Assessment of Aims and Objectives:**

The **first primary objective** will be assessed by examining cellular and humoral immune responses using plasma and PBMC from a 10 mL venous bleed collected at the cessation of drug treatment.

The **second primary objective** will involve relating immune responses measured at the cessation of drug treatment with the incidence of *P. falciparum* and *P. vivax* infections and disease in the subsequent 8 months as determined under Aim 1.

**The secondary objectives will be assessed as follows:**

- PBMC and serological assays will be performed on samples acquired after the cessation of the drug treatment regimes to evaluate the impact of clearing liver and blood-stage infections vs clearing blood-stage infections only, on cellular and humoral immune responses.
- PBMC and serological assays performed on baseline samples of the Mugil treatment-re-infection study will be applied to the above mentioned samples in this study to compared cellular and humoral responses in the two cohorts and confirm previous associations between immune responses and protection.

## 4 STUDY DESIGN

In this study 500-600 children aged 5-10 years will be screened, enrolled and randomized to 2 arms of a longitudinal cohort study. The randomized arms will comprise:

- 250-300 children pre-treated with 3 days Chloroquine (CQ), 4 weeks Primaquine (PQ) and 3 days Coartem (CO)
- 250-300 children pre-treated with 3 days Chloroquine (CQ), 4 weeks Placebo (PL) and 3 days Coartem (CO)

At enrolment all eligible children aged 5-10 years in the study area will be screened for Glucose-6-Phosphate Dehydrogenase deficiency (G-6-PD) and the presence of severe anaemia or malnutrition. Children with less than 60% G-6-PD activity, haemoglobin <5g/dl or severe malnutrition (weight-for-age nutritional Z score [WAZ] <60th percentile) will be excluded from the study. All other children will be randomized to the two treatment arms of the study.

Drug treatment will commence at enrolment. All children will receive CQ on days 1-3. Children will also receive either PQ (0.5 mg/kg) or placebo on days 1-5, 8-12, 15-19 and 22-26 (i.e. Monday to Friday for 4 weeks). During the third week of drug treatment all children will receive CO on days 15-17 (according to national treatment guidelines). Children will be actively monitored for side effects including measurement of haemoglobin levels at days 1, 8, 15 and 22.

Following completion of treatment, children will undergo a clinical examination and a 10 mL venous blood sample will be collected on day 29 (i.e. 26 days after their last dose of CQ, 12 days after their last dose of CO and 3 days after their last dose of PQ or PL).

Subsequently, all enrolled children will be followed using 2-weekly active and continuous passive case detection at a local health centre for 8 months (Week 2-32). Active follow-up consists of morbidity surveillance visits to monitor clinical malaria illness not reported to a health facility, as well as blood sampling for the detection of asymptomatic malaria. These visits will include collection of a medical history of the preceding 2 weeks to determine incidence of malarial infections and bed net usage, a physical examination, measurement of axillary temperature. A 250µl finger prick blood sample will be collected every 2 weeks for the first 12 weeks and 4 weekly thereafter, i.e. weeks 2, 4, 6, 8, 10, 12, 16, 20, 24, 28 and 32.

All blood samples will be assessed for the presence, type, and number of malarial infections (by light microscopy and PCR) and Hb levels. The 10 mL venous blood samples will also be used for the assessment of humoral and cellular immune responses to *Plasmodium* infections (Aim 2). DNA

extracted from venous blood samples and the finger-prick blood samples collected during follow-up will be assessed in molecular parasitology studies (Aim 1).

During the entire study period, a passive case detection system will be maintained at the local Health Centre. Every participating child that presents at the health centre with a febrile illness will be clinically assessed and have a finger prick blood sample taken for determination of malaria infections by a Rapid Diagnostic Test (RDT), two blood slides for microscopy confirmation and HemoCue® for Hb concentration. In accordance with the new national treatment guidelines, only children with a positive RDT will receive Coartem treatment from the attending field Nurse. All the data collected will be recorded in the morbidity forms and the health book of each participating child to be reviewed by the study clinician.

Over the 9-month study duration, each participant will have 38 contacts with the study team (1 for enrolment/screening, 20 for supervision of drug administration, 1 baseline time-points (after drug treatment), 16 active follow-up visits) and will be asked to contribute one 10 mL venous blood sample at the baseline visit and 12 finger prick blood samples (250µL) (see Study Schedule Diagram, Appendix I.) Additional finger prick blood samples may be collected at the time of febrile illness during morbidity follow-ups and passive case detection.

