#### **6.1.2 Enrollment and Screening**

Community awareness will be carried out through community leaders, village elders, health authorities, and village Reporters in the study area. An Information session for the parents of participating children will then be organized in the villages in the form of meetings to brief them on the broad aims and objectives of the study. After these meetings, a census of eligible children in the study area will be carried out before a formal informed consent is obtained (see section 6.0) from the parents to enroll their children in the study.

Following these consultations prospective participants will be screened for their suitability for inclusion in the study. After obtaining informed consent from parents or legal guardians, children will be screened for eligibility and their demographic (age, sex) and anthropometric data (weight) recorded and Hb levels determined. In order to prevent treating children with G-6-PD deficiency with primaquine, all children will be tested for G-6-PD deficiency at time of enrollment. All eligible children will be assigned a unique PNGIMR identification number. This number will be used to identify that child for the duration of the study.

Children with reported symptomatic illness will be examined by the study team and treated as required. In children with presumptive malaria illness the illness will be diagnosed on the spot using a rapid malarial diagnostic test (RDT). Children with a positive RDT test and/or and Hb < 8 g/dL will be treated with a full course of Coartem in addition to the albendazole and oral iron supplementation.

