### **6.1.7 Passive case detection**

The schools in the study are within less than 10km (i.e. up to 3 hours walk) of Albinama health centre. The health centre has both in-patient facilities and is staffed with a health extension officer and several nurses and community health workers. The health centre staff routinely assesses patients for malaria and upper respiratory tract infections (the 2 most common reasons for seeking treatment). As at all other PNG health centres, attendance and admittance log books are kept.

The study team will coordinate with the health centre nursing staff for the collection of illness and treatment histories of study participants on special Health Centre Surveillance Forms. The health centre staff will be requested to screen incoming patients who are between 5-10 years of age in order to determine if they are study participants. If the health centre staff identifies the incoming patient as a study participant, the nursing staff will refer the patient to a health centre based study nurse. The nurse will take detailed history, fill in the Health Centre Surveillance form, do a finger prick blood sample to obtain blood smears and for determination of infecting malaria species, measure Hb and confirm the presumptive diagnosis using RDT, unless the child has received malaria treatment in the previous 2 week period. For children excluded from undertaking RDT tests, blood smears will be read overnight for malaria diagnosis. In the case of a positive RDT or positive blood smear or, a Hb <8.0g/dL, the child will be treated with a locally available appropriate antimalarial treatment and iron supplementation by the study nurse.

Results of RDT and Hb measurement will be passed onto health centre staff. For children with negative RDT the health centre staff will be advised to refine the diagnosis for other febrile illnesses and treat accordingly.

All health centre visits will be recorded in the child's health booklet, which will be cross-checked at the active morbidity surveillance time points.

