#### **6.1.8.1 Blood Smear Confirmation of RDT-based Diagnosis**

Blood smears from all symptomatic children made during the study visits by the field study team will be read overnight by the Microscopist at the PNGIMR's Maprik field station to confirm RDT diagnosis. Should smear results show the presence of malarial parasites in children with negative RDT results, the study team will search out the children and initiate treatment with Coartem.

Blood slides from asymptomatic children will be read retrospectively.

Results from all smears will be entered onto the study's microscopy results form and subsequently entered into the study database.

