#### **6.1.8.3 Diagnosis and Treatment**

All participants diagnosed with presumptive malaria by health center staff will be referred to the health centre based IMR nurse. The IMR nurse will take detailed history, fill in the Health Center Surveillance form, do a finger-stick blood sample to obtain blood smears, measure Hb and confirm the presumptive diagnosis using a RDT, unless the child has received malaria treatment in the previous 2 week period. . For children excluded from undertaking RDT tests, blood smears will be read overnight for malaria diagnosis. In the case of a positive RDT or positive blood smear or, an Hb <8.0 g/dL the child will be treated with a locally appropriate antimalarial treatment and iron supplementation by the IMR nurse.

Results of RDT and Hb measurement will be passed on to health center staff. For children with negative RDT the health center staff will be advised to refine the diagnosis for other febrile illnesses and treat accordingly.

The PNG Institute of Medical Research will be fully responsible for maintaining the presence of a fully register nursing practitioner at Albinama Health Centre and for all treatments dispensed through the IMR nurse.

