**Follow-up and Morbidity Surveillance**

Finger prick blood samples of approximately 200 -250 µL will be collected every two weeks for the first 12 weeks and 4 weekly thereafter from each child participating in the study. Additional samples will be taken from symptomatic individuals at both active and passive morbidity surveillance visits. Blood samples will be obtained by the finger-stick method. This sample will provide adequate blood for the preparation of thin/thick blood smears to detect the presence of malaria parasites, type of malaria parasites, and level of parasitaemia. At baseline and the final visit, part of the sample will also be used to determine Hb concentration. The samples collected in microtainers will be processed into cell pellet (for DNA preparation, PCR/LDR-based diagnosis of malaria parasites and Duffy genotyping) and plasma (for immunological investigations).

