#### **11.1.2.3 Time to first *P. falciparum* / *P. vivax* infection**

For the analyses of time to first *P. falciparum* / *P. vivax* infection children will be at risk until they either experience a *P. falciparum* / *P. vivax* infection or they are treated with antimalarial drug for another malarial infection. At the time of the first antimalarial treatment, the child will be censored from analysis.

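### The protocol gives two rules for treating an RDT-negative child at the health centre and two wordings for when treatment censors time to first infection; they diverge for a child treated on low Hb alone.

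*Protocol*

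**What the plan says.** **Treatment at the health centre.** Section 4 has each febrile participant tested by RDT, with two slides and a HemoCue reading, and then says that "only children with a positive RDT will receive Coartem treatment from the attending field Nurse". Section 6.1.7 covers the same health centre and the study nurse based there: "In the case of a positive RDT or positive blood smear or, a Hb <8.0g/dL, the child will be treated". The child is to be "treated with a locally available appropriate antimalarial treatment and iron supplementation by the study nurse". Section 6.1.8.3 repeats this for the same nurse: "In the case of a positive RDT or positive blood smear or, an Hb <8.0 g/dL the child will be treated".

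**Treatment elsewhere.** Sections 6.1.5 (baseline visit) and 6.1.6 (active visits) carry the same three-way trigger. Section 6.1.8.1 adds, for symptomatic children seen at study visits: "Should smear results show the presence of malarial parasites in children with negative RDT results, the study team will search out the children", and Coartem is then started.

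**Hb measurement.** Section 4 has Hb assessed in every blood sample. Section 6.1.8 lists it for children with RDT-confirmed infection or clinical signs of anaemia. Section 6.2.2.1.1, under Follow-up and Morbidity Surveillance, says: "At baseline and the final visit, part of the sample will also be used to determine Hb concentration".

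**Censoring.** Section 8.1.1 puts time to first *P. vivax* and *P. falciparum* infection first among the primary outcomes. Section 11.1.2.3 keeps a child at risk until infection or until treated for a different malarial infection. It then adds: "At the time of the first antimalarial treatment, the child will be censored from analysis".

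**The concern.** Treatment outside the randomised pre-treatment course ends risk time for a primary endpoint, so the rule that decides who is treated also helps decide who is censored and when. If the treatment rule, the Hb measurement that feeds it and the censoring rule are each stated in more than one way, an RDT-negative child's care and observed time depend on which section the nurse and the analyst follow.

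The Hb limb deserves most attention. Treatment for a positive RDT or smear at least reflects infection. Treatment for low Hb need not, and low Hb can be an effect of the randomised drug: Section 2.3.1 notes haemolytic anaemia in G-6-PD deficiency, and Section 6.1.4 monitors Hb for a haemolytic reaction to primaquine. Censoring on that basis may be informative and may not be equally frequent in the two arms.

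**Working it through.** The protocol states no figure on this point, so the check is mainly a comparison of passages.

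**1. Who is treated at the health centre**

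| Symptomatic child | Section 4 | Sections 6.1.7 and 6.1.8.3 |
|---|---|---|
| RDT positive | treated, Coartem | treated, drug unnamed |
| RDT negative, smear positive | not treated | treated |
| RDT negative, smear negative, Hb <8.0 g/dL | not treated | treated |

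The second and third rows conflict, for the same place and the same nurse.

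**2. Who can meet the Hb trigger.** Under Section 4 Hb is known for every sampled child. Under Section 6.1.8 an RDT-negative child without clinical signs of anaemia has none taken. Section 6.2.2.1.1 mentions Hb for the baseline and final scheduled samples; it does not bar measurement at other times. Sections 6.1.6, 6.1.7 and 6.1.8.3 measure Hb in children thought to have malaria.

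**3. What treatment does to time to first infection (Section 11.1.2.3)**

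| Reason for treatment | If risk time ends at treatment for another infection | If risk time ends at any antimalarial treatment |
|---|---|---|
| Smear positive for the species analysed | event | event |
| Malaria of another species | censored | censored |
| Hb <8.0 g/dL alone, no infection detected | not clearly censored | censored |

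Only the last row depends on the wording.

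**4. Which endpoints are reached.** Sections 11.1.2.1 and 11.1.2.2 end risk time at the endpoint, withdrawal, loss to follow-up, completion or two consecutive missed visits. Treatment is not listed. The censoring problem is therefore confined to time to first infection.

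**5. Could it differ by arm?** From Section 4, primaquine or placebo ends on day 26 and the baseline visit is on day 29: 29 − 26 = 3 days. The last scheduled Hb check in treatment is day 22: 29 − 22 = 7 days before baseline, with doses on days 22 to 26 given on or after that check. Section 2.3.1 randomises children with 60–80% G-6-PD activity. A fall in Hb first seen at baseline in a symptomatic child would lead to Coartem under Section 6.1.5 and, if any antimalarial treatment censors, leave that child with no follow-up time.

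**6. Power (illustration on assumed rates).** Take 200 children per arm, follow-up T = 224 days, and the medians and hazard ratios (HR) of Section 11.2.1 before its bednet adjustment. Assume exponential times, an independent treatment-censoring rate c, and two-sided 5% (no alpha is stated).

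Expected events per arm = 200 × λ/(λ + c) × (1 − exp(−(λ + c)T)), with λ = ln 2/median in the placebo arm and λ × HR in the primaquine arm. With D the events in both arms, power = Φ(½ √D × |ln HR| − 1.96).

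| c per child-year | PCR (HR 0.70, median 54 d): events, power | LM (HR 0.66, median 118 d): events, power |
|---|---|---|
| 0 | 362, 92.4% | 262, 92.0% |
| 0.25 | 345, 91.2% | 247, 90.4% |
| 0.5 | 330, 89.9% | 232, 88.6% |
| 1.0 | 302, 87.3% | 207, 84.9% |

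A rate of 0.25 corresponds to 1 − exp(−0.25 × 224/365.25) = 14% of children over follow-up, before allowing for infection. Its cost is 1.2 points (PCR) and 1.6 points (LM). With the medians halved or doubled it is 0.6 to 2.2 points (PCR) and 0.6 to 2.8 points (LM). These rates cover all treatment censoring, of which the Hb-alone group is only a part. The illustration says nothing about bias, because it assumes censoring unrelated to infection risk.

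**The case against.** Much can be said in the plan's favour.

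- **One outlier, not many rules.** Sections 6.1.5, 6.1.6, 6.1.7 and 6.1.8.3 state one three-way trigger, and 6.1.8.1 is consistent with its smear limb. The exception is one sentence in the Section 4 overview. That sentence can be read as an on-the-spot rule with smears read later, and the smear limb in 6.1.7 as meant for children who are not given an RDT. Both readings soften the smear conflict. Neither fits the word only in Section 4 with treatment on Hb, so the conflict stands.
- **Hb below 8.0 g/dL might be taken as a screen of every child.** The documents do not support that. In each of these sections the trigger follows a description of children with symptoms or presumed malaria.
- **Haemolysis might be thought to censor many primaquine children.** Section 6.1.4 removes children with adverse reactions from further pre-treatment and from the study, Hb is checked on days 1, 8, 15 and 22, and children below 60% G-6-PD activity are excluded. What remains is a fall that was missed or came after the day 22 check.
- **The second censoring sentence may simply refer back to the first.** That is a natural reading, so this is ambiguity rather than flat contradiction. It still leaves the Hb-alone child undecided.
- **Sensitivity analyses belong in a SAP.** True in general, but a reason for treatment that was not recorded at the time may not be recoverable, and the protocol itself has stated the censoring rule in two ways.

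**Conclusion.** The point holds in limited form. Section 4 cannot be followed together with Sections 6.1.7 and 6.1.8.3 for an RDT-negative child. The Hb measurement rules differ between sections. The censoring trigger in Section 11.1.2.3 is open for a symptomatic child treated on Hb alone.

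The statistical reach is one primary outcome, time to first infection; the incidence outcomes are not censored at treatment. Censoring could differ by arm, but the effect is probably small, and neither its size nor its direction can be derived: the documents give no frequency of Hb below 8.0 g/dL or of RDT-negative, smear-positive illness. A reader might infer that the primary comparison is biased or short of power for this reason. The documents do not show the first. On the second, the illustration suggests a modest loss even when all treatment censoring is counted. The case for correction rests on unclear care and possibly informative censoring, and on how little the correction costs.

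**What to change.** 1. The clinical team should reconcile Sections 4, 6.1.5, 6.1.6, 6.1.7, 6.1.8, 6.1.8.1, 6.1.8.3 and 6.2.2.1.1 into one treatment rule and one Hb-measurement rule. This review takes no view on which rule is right.
2. State a single censoring trigger in Section 11.1.2.3 that says explicitly what happens to a child given an antimalarial with no infection detected.
3. Record the reason for every antimalarial course: RDT, smear, or Hb alone.
4. Repeat the time-to-first-infection analysis without censoring children treated on Hb alone.

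The cost is protocol wording, one field on existing forms and one sensitivity analysis. No added visits, samples or children are needed for the censoring and recording changes.

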## 5 STUDY POPULATION

### 5.1 Selection of the Study Population

Data from both active and passive morbidity surveillance in the Wosera area show that the incidence of both *P. falciparum* and *P. vivax* malaria is greatest in the 1- to 5-year old age group but remains a significant burden in the 5-10 year old age bracket, during which time the children are acquiring clinical immunity, particularly to episodes of *P. falciparum*. A recent study in Madang (10) showed that in an area of hyperendemic transmission children of the 6-12 year age group had already acquired a high degree of clinical immunity to *P. vivax* but were still experiencing significant numbers of *P. falciparum* clinical episodes despite similar incidence of new blood stage infections.

This study will thus be done in children 5-10 years of age ( $\pm 3$  months). This age group is selected because:

- a) Children in this age group have acquired a sufficient degree of immunity to exert a significant amount of control on parasite but are still at significant risk of symptomatic illness with at least *P. falciparum*.
- b) An earlier study in a similar age group (5-12) in Madang showed that this age group is thus ideal for determination of immunological correlates of natural acquisition of immunity to *P. falciparum*. A 2nd study in the same age group is now required will allow findings from a similar study north of Madang to be confirmed in a children in a different region of PNG.
- c) This will allow for an extension of a previous liver-stage/blood-stage treatment to re-infection study into slightly older children. Together these studies will cover the entire age range (1-10 yrs) from non-immune to highly clinically immune.
- d) The lower number of clinical episodes in this age group will allow to study the dynamics of acquisition and loss of individual *P. falciparum* and *P. vivax* infections in semi-immune individual in the absences of frequent drug treatment.

The study will enroll 500-600 children with approximately the same numbers of male and females. All study participants will be ethnic Melanesian.

Children will be recruited from elementary schools in the vicinity of the Albimana health center (see Figure 3 in Section 5.2). Albimana is an ideal study location. It has a similar malaria prevalence rate as the neighboring Ilaita area and is accessible by road all year round.

Before commencing the project, the study team will hold community information meetings and conduct a baseline census in all potential study villages and thereby obtain a list of families who have eligible children. These families will then be contacted and invited to take part in the study.

See Section 6.0 Informed Consent Process for details on how families will be contacted.

[figure not shown]

